**1. SUMMARY**

Intermittent preventive treatment in children (IPTc) is a promising new approach to malaria control. This approach involves giving anti-malarial drugs to 3-59 month old children at defined periods annually. Studies in Senegal and Mali show that IPTc can reduce the burden of malaria in children substantially in the Sahel and sub-Sahel regions of West Africa. It is unclear which will be the most appropriate delivery system for IPTc under routine programme conditions in order to achieve both equitable and sustainable coverage, and to maximise adherence to IPTc regimes. We propose a pilot study on ways in which IPTc can be scaled-up in routine programme conditions. The coverage of IPTc (four treatment courses of amodiaquine+ sulphadoxine-pyrimethamine during the rainy season) achieved by a network of community based volunteers will be compared to that achieved by routine Health centre and EPI/growth monitoring staff in a randomised trial. Five health centres and their catchment population will be randomly allocated to one these two approaches. The outcomes of the study will be measured by pre- and post intervention cross sectional surveys.

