**7.4 Sample size**

The sample size calculation for the primary end-point takes into account that the village and not the individual, is the unit of randomization. The number of villages required for the trial depends on the expected compliances in the village based and health centre based delivery systems, the variability in compliance between villages and the number of participating children in each village. Assuming 80% compliance in the community based IPTc delivery system and 45% or worse compliance in health centre based delivery system with a coefficient of variation between villages of 0.25, assuming that there are 60-100 children in each village, 5 villages or cluster of villages in each arm will be needed for the study. Such a study will have 80% power at 5% level of significance to show a difference in compliance.

All children eligible and their parents consented to participate in the study will be recruited. The recruited children (600-1000) will be included in the cross-sectional surveys at the beginning and end of the intervention.

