**7. 5 Enumeration, recruitment and consent**

Five villages with an average population of 80 children aged less than five years will be allocated to receive IPTc distributed by health staff from five health centres. Five villages of the same size will be selected to receive IPTc from a community-based IPTc coordinator.

Once villages have been chosen in April 2006, several meetings with all potential partners (health authorities, community leaders and care givers) will be held. Meetings will be held with the district health directorate staff and assembly members from the district administration. We will then hold meetings with the chiefs and elders, opinion leaders and parents or guardians of prospective study subjects in the villages selected. Explanations will be provided to opinion leaders and parents in local languages, emphasising the potential public health impact of the study for malaria control. They will be provided with information sheets in English or in the appropriate local language (Ewe or Akan).

Enumeration of all children aged between 3-59months of age in the study area will be carried out in April 2006 and a database established before the start of the study.

Approximately, 960 children will be eligible for enrolment in the study. Enrolled subjects will be provided with an identification card on which their names, age, sex, weight at enrolment, drug code mother/guardian’s name and study number will be written to facilitate identification at each contact.

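### The protocol names two different units of randomisation, five health centres or ten villages, and the 80% power holds only for the villages

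*Protocol*

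**What the plan says.** Four places in the Protocol bear on what is randomised.

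- **Section 1, Summary:** "Five health centres and their catchment population will be randomly allocated to one these two approaches". The unit is the health centre with its catchment, and there are five in all.
- **Section 7.4, Sample size:** "the village and not the individual, is the unit of randomization", and "5 villages or cluster of villages in each arm will be needed for the study". The unit is the village (or a group of villages), and there are ten in all.
- **Section 7.5, Enumeration, recruitment and consent:** five villages are assigned to delivery by staff of five health centres, then "Five villages of the same size will be selected to receive IPTc from a community-based IPTc coordinator". No random step is described for either set.
- **Section 7.13, Data management and analysis:** the primary comparison is between the five villages of the health centre group and those of the community group.

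Section 7.1 (Trial Design) calls the trial open label with two arms and names no unit. Section 6.2 gives the district eight health centres.

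**The concern.** The unit of allocation fixes the number of independent observations, the degrees of freedom and the valid test for the primary comparison. Ten units support the calculation in 7.4. Five units do not, because the error degrees of freedom fall from 8 to 3 and one arm has only two clusters.

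The two descriptions cannot be merged by a generous reading:

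- Five health centres per arm would need ten, and the district has eight.
- Treating each catchment as the village cluster allowed by 7.4 still leaves five clusters in all, where 7.4 requires five per arm.
- If centres were randomised and two villages taken from each, villages sharing a centre would not be independent, and the village-level calculation would not apply.

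The wording of 7.5 adds to the problem. It is the operational section on choosing villages, and it does not say that chance decides which village goes to which arm. A mistake at this step cannot be repaired at analysis.

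**Working it through.** **Inputs, all from section 7.4 unless noted**

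- Community arm: "Assuming 80% compliance in the community based IPTc delivery system", so p1 = 0.80.
- Facility arm: "45% or worse compliance in health centre based delivery system", so p2 = 0.45 and the difference is 0.35.
- Between-village CV: "with a coefficient of variation between villages of 0.25", so k = 0.25.
- Children per village: m = 60 to 100; 7.5 gives an average of 80.
- Power 80%, significance 5%. Two-sided is assumed, as the protocol does not say.

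**Step 1. Reproduce the protocol's figure.** The usual formula for clusters per arm with proportions is

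c = 1 + (1.96 + 0.84)² × [p1(1−p1)/m + p2(1−p2)/m + k²(p1² + p2²)] / (p1−p2)²

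Here (1.96 + 0.84)² is about 7.85. For m = 80:

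- p1(1−p1)/m = 0.16/80 = 0.0020
- p2(1−p2)/m = 0.2475/80 = 0.0031
- k²(p1² + p2²) = 0.0625 × (0.64 + 0.2025) = 0.0527
- c = 1 + 7.85 × 0.05775/0.1225 = 4.70

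| Children per village | c | Rounded up |
| --- | --- | --- |
| 60 | 4.81 | 5 |
| 80 | 4.70 | 5 |
| 100 | 4.63 | 5 |

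Five per arm is reproduced.

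**Step 2. Power of 5 v 5 villages.** The variance of a cluster proportion is p(1−p)/m + k²p². For m = 80 this is 0.0420 (community) and 0.01575 (facility).

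- SE of the difference = √(0.0420/5 + 0.01575/5) = 0.1075
- Non-centrality = 0.35/0.1075 = 3.26
- Power (non-central t, 8 df) = 81%

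Over m = 60 to 100 the power is 80-82%. A beta-binomial simulation with a t-test on village proportions gives 75-76%, a little lower. The 80% claim is sound for this design.

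**Step 3. Power of five health centres, 2 v 3.** Two further assumptions are needed. The catchment size is taken as 10 × 80/5 = 160 study children. The CV between catchments is not given anywhere, so 0.25 is borrowed from villages and then varied. At CV 0.25 the cluster variances are 0.0410 and 0.0142.

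- Two community, three facility: SE = √(0.0410/2 + 0.0142/3) = 0.159; non-centrality 2.20; power (3 df) 34%.
- Three community, two facility: SE = √(0.0410/3 + 0.0142/2) = 0.144; non-centrality 2.43; power (3 df) 39%.

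| Assumed CV between catchments | Power, 2 v 3 (non-central t, 3 df) |
| --- | --- |
| 0.25 | 34-39% |
| 0.20 | 46-53% |
| 0.15 | 66-73% |
| 0.10 | 90-93% |

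More children do not help much: at CV 0.25 with unlimited children per catchment, power is 35-41%. The method matters with so few clusters. At CV 0.25 and 60 to 100 children per cluster, the simulated t-test gives about 40-49%, against 32-38% by non-central t.

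**Step 4. Randomisation test.** Five units split 2 v 3 have C(5,2) = 10 possible allocations, so the smallest attainable p is 1/10 = 0.10. This holds whatever the CV. For 5 v 5 the smallest two-sided p is 2/C(10,5) = 2/252 = 0.008.

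**Step 5. Number of children.** Section 7.5 implies 10 × 80 = 800 children but also says "Approximately, 960 children will be eligible for enrolment in the study". At 96 per village instead of 80, power for 5 v 5 moves from 81% to 82%.

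**The case against.** The strongest reply is that only one sentence is out of line. Sections 7.4, 7.5 and 7.13 all work with five villages per arm. Section 7.1 has EPI nurses supplying both health centre staff and community coordinators in their catchment areas, and the budget justification lists five EPI nurses. This fits five catchments that each host both delivery systems, with the Summary loosely worded. No operational section describes two centres against three, and the 2 v 3 split is an inference from five units and two arms. All of this stands, and it is a good reason to settle on the village. It does not remove the conflict, because the only explicit statement of random allocation is the Summary's, and it names the health centre.

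Four stronger readings are tempting and are not supported:

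- **That the 80% power is miscalculated.** It reproduces for the design that 7.4 describes.
- **That the trial's power is 34-39% on the protocol's own inputs.** Section 7.4 gives the CV between villages only. Between catchments it is unknown, and the result depends strongly on it.
- **That the community villages were to be hand-picked.** The Summary calls the trial randomised and 7.4 speaks of a unit of randomisation. The wording of 7.5 is loose and should be made explicit, but it is not evidence of purposive choice.
- **That 960 eligible children is an error to be cut to 800.** Section 7.4 allows 600 to 1000, so 960 is within the protocol's own range. It disagrees only with the average of 80 in 7.5.

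**Conclusion.** The protocol contradicts itself on the unit of randomisation, and this needs to be resolved before any allocation is made. The 80% power is right for ten independently randomised villages (80-82% by t with 8 df). It cannot be claimed for five health centres. There, power is about 34-39% if the CV between catchments is 0.25, and reaches 80% only if that CV is well below the village value: 66-73% at 0.15 and 90-93% at 0.10. These figures assume about 160 children per catchment, a two-sided 5% test and the most even split. The floor of p = 0.10 for a 2 v 3 randomisation test needs no assumption about the CV.

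The mismatch between 960 and 800 children is a minor note with almost no effect on power.

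**What to change.** Use one statement in the Summary and in 7.5, consistent with 7.4 and 7.13: *ten listed villages are randomised 5:5 to the two delivery systems; the village is the unit of randomisation and analysis*. In 7.5 this replaces the separate descriptions of how each arm's villages are obtained.

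If the health centre is in fact the unit, withdraw the 80% claim in 7.4 and restate power for five clusters. State the between-catchment CV as an assumption and show a range; a single figure such as 34-39% should not be written in as if it were known. Sections 7.4, 7.5 and 7.13 would then need to follow the Summary.

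As a minor tidy-up, bring the average of 80 per village and the 960 eligible children in 7.5 into agreement.

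The cost is wording and one random draw. The real downside of randomising villages is that two villages sharing a catchment and an EPI nurse may be in different arms, so some contamination of coverage is possible. The identification card (Appendix 3) records the assigned group and the dates of administration but not which system delivered each course, so it cannot show cross-over by itself. The delivering system should be recorded for each course on the drug distribution form already collected under 7.8, if it is not there already.

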**2.0 BACKGROUND TO THE STUDY**

2.1 **Introduction**

It is estimated that in 2002, 400 million episodes of clinical malaria occurred in sub-Saharan Africa (Snow et al et al, 2005) and 94% of global deaths attributable to malaria occurred in this region (Bryce et al. 2005). One promising approach is the administration of intermittent preventive treatment for malaria (IPT) to infants (IPTi) or to children under five years old (IPTc), which involves administration of a predefined number of treatment courses of antimalarial drugs at specified time intervals. Administration of sulfadoxine/pyrimethamine (SP) to infants at the time of the second and third DPT and measles vaccinations reduced the incidence of malaria by 59% in an area with perennial transmission in Tanzania (schellenberg et al. 2001). However, in an area with highly seasonal transmission of malaria in Ghana SP-IPTi reduced the incidence of malaria by only 25% (Chandramohan et al. 2005). This marked variation in the protective efficacy of IPTi in Tanzania and Ghana is primarily due to the differences in the transmission dynamics of malaria between West and East Africa. In highly seasonal transmission areas of West Africa targeting IPT during the high transmission season is more appropriate than administering IPT throughout the year. Furthermore the IPTi strategy cannot be the solution for large-scale malaria control in many parts of Africa where the burden of the disease is not predominantly in infants. There is now growing evidence that season IPTc can reduce the burden of malaria substantially in Sahelian West Africa. Three courses of SP and artesunate during the high transmission season to <5 year old children reduced the incidence of malaria by 86% in Senegal (Cisse et al in press) and 40% in Mali (Dicko et al.2004).

Although there is a strong evidence base for introducing an IPTc programme, there are concerns about sustainable approaches to delivering IPTc. Community volunteers based delivery systems have been used successfully in onchocerciasis (Katabarwa et al. 2001), filariasis (Ramaiah et al. 2001), schistosomiasis (Katabarwa et al. 2005), and trachoma mass drug delivery programmes. Another option is to deliver IPTc during routine EPI/growth monitoring clinic visits. The coverage of EPI vaccination is low in many countries of West Africa in comparison to those of East and Southern Africa (Webster et al. 2005); however, in Ghana approximately 70% of 1 year olds are fully protected by all EPI vaccines. Growth monitoring visits in Ghana are higher amongst one year old children than those over one year, which may be due to the link with EPI vaccination under one year of age. It is possible to encourage caretakers to attend growth monitoring clinics through targeting health education and changing their perception of the values of these child welfare clinics. However, offering IPTc during growth monitoring visits might have an incremental positive effect and encourage caretakers to use these clinics more regularly. Conversely, it is also plausible that the increased workload of the health services staff due to this integrated delivery of IPTc and growth monitoring may lead to programme fatigue.

Ensuring that the correct amount of drugs are delivered to the target children at the most appropriate time of the year, and sustaining adherence to the treatment regimes through any delivery systems is a challenge. However, these challenges are not insurmountable and different ways of delivering IPTc need to be explored. Thus we propose to evaluate two different approaches to delivering IPTc.

**3.0 STUDY OBJECTIVES**

- 1. **Primary objective**

To compare the coverage of IPTc achieved through two different delivery systems.

- 1. **Secondary Objective**

To compare the level of adherence to the IPTc regime in the two delivery systems

To assess the impact of IPTc on the incidence of malaria

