**5.2 Secondary end-points:**

1. Proportion of IPTc courses completed per protocol (adherence to treatment regime)
2. Incidence of clinical malaria
3. Prevalence of malaria parasitaemia at the end of the rainy season.

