**7.0 STUDY DESIGN AND METHODOLOGY**

**7.1 Trial Design**:

An open label trial with two arms: (1) Health facility based IPTc; (2) community based IPTc. Children in both arms will receive four courses of AQ+SP (a three day regime) in May, June, September and October (Figure 1). The EPI nurses will collect drugs from the District Health Directorate (DHD) when collecting vaccines and family planning devices for their outreach activities. The nurses will transport and deliver the drugs to the health centre staff and community-based IPTc coordinators in their catchment areas for distribution. They will also carry out health education activities about IPTc during child welfare clinics in the communities. The schedule for drug administration and number of doses per child in a year will be designed in the child’s road to health card. EPI nurses will pass on information through mothers/guardians who attend child welfare clinics or through their routine contact persons in the communities on scheduled days for drug distribution.

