**7.7 Cross-sectional surveys**

Two cross-sectional surveys will be undertaken in May and November 2006. The first survey will be the pre-intervention survey which will provide baseline information about the study children and the second one will be a post- intervention survey. In both surveys, information to be collected will include the background information about the child and mother/guardian, history of allergy to any of the study drugs, bednet ownership and use, measurement of temperature and anthropometric indices. This will also involve collection of finger prick blood samples for determination of asexual and sexual parasitaemia.

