**7.9 Surveillance during the period of intervention**

A passive surveillance system to monitor malaria episodes in study children will be set up in the health centres within the catchment areas of the IPTc communities and in the district hospital.

Parents and guardians will be advised to come directly to a health centre if their child developed any symptoms or signs of illness. If the child has fever or any features suggestive of malaria, a finger prick blood sample will be collected for malaria parasite before treatment will be given. One slide will be prepared for each child and the slides will transported to a central laboratory for double reading and for definitive diagnosis. Those who test positive for malaria will be treated with oral quinine 10mg/kg 8hourly for 7days and will be followed on days 3 and 7 for outcome. Health centres with laboratory services, will collect blood sample for Hb. Children with Hb<8.0g/dl will receive treatment for anaemia. Every participating child who presents to the health facility for medication will be asked to produce an ID card. The information on the ID card will be compared with the master list held by the surveillance staff. Treatment at the health facility for malaria and anaemia will be free for all participating children.

Records will be kept of all admission and deaths of study children at the district hospital. A physician or a medical assistant and nurses on the ward will be asked to look out for any child with severe malaria, and any admission attributed to malaria will be carefully documented.

A surveillance supervisor will visit the health facilities fortnightly from June to October to supply logistics and collect completed record forms and prepared slides. At the same time s/he will visit IPTc coordinators to collect completed forms on community deaths. All deaths will be investigated using post-mortem questionnaire techniques and cause of death established wherever possible. The ID card will be used to confirm the identity of the deceased child and may provide some important information about the health and nutritional status of the child prior to death.

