**Training and Capacity Development:**

Amodiaquine plus artesunate combination is the leading option for Ghana for treatment of malaria. There is evidence that AQ+AS is an alternative to SP for IPTc. Obtaining evidence of efficacy of AQ+SP will provide an alternative to AQ+AS for IPTc before implementation as policy

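### The secondary objective on the impact of IPTc on malaria incidence is not directly estimable, because both arms receive IPTc and no incidence is recorded without it

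*Protocol*

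**What the plan says.** Section 3.0 (Study Objectives) lists two secondary objectives. One compares adherence between the delivery systems. The other is worded differently: "To assess the impact of IPTc on the incidence of malaria". It names the effect of IPTc itself, not a difference between systems. The matching end-point in section 5.2 is "Incidence of clinical malaria".

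Section 7.1 (Trial Design) describes "An open label trial with two arms: (1) Health facility based IPTc; (2) community based IPTc", and adds that "Children in both arms will receive four courses of AQ+SP". Section 4.0 confirms that the arms differ in who delivers the drug and where. No placebo, untreated or delayed group is described anywhere.

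Incidence data come from section 7.9, headed as surveillance during the intervention: "A passive surveillance system to monitor malaria episodes in study children will be set up in the health centres". The timetable lists this surveillance as starting in June 2006, the month in which section 7.8 starts drug administration.

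The only measurement planned before treatment is the first of the two surveys in section 7.7: "Two cross-sectional surveys will be undertaken in May and November 2006". These surveys collect finger-prick blood for parasitaemia.

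Separately, the Training and Capacity Development paragraph says: "Obtaining evidence of efficacy of AQ+SP will provide an alternative to AQ+AS for IPTc before implementation as policy".

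**The concern.** To estimate the impact of IPTc on incidence, the trial needs incidence with IPTc and incidence without it, measured in a comparable way. The protocol plans only the first. An analysis plan can choose among analyses, but it cannot supply a missing comparator, so the problem lies in the objective as the protocol states it.

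At stake is what the trial may conclude. A difference in incidence between arms would reflect the gap in uptake between two delivery systems. If both systems delivered well, the arms would look alike, and a reader holding the report against the stated objective could take that as no impact of IPTc.

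**Working it through.** **1. Candidate comparisons, set against the objective**

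- *Between arms.* This is randomised and concurrent, but both arms are treated (sections 4.0 and 7.1). It estimates delivery system, not IPTc against none.
- *Before and after, incidence.* Not available. Surveillance and drug administration are both listed from June 2006 (section 7.8, timetable). The timetable grid marks both from month 5, which gives no lead-in either. Suppose the grid's May mark for surveillance is paired with the June drug start in section 7.8. That leaves at most about one month at the start of the season, with no concurrent control. Section 7.1 also lists a May course, so the passages on timing need to be reconciled in any case.
- *Before and after, prevalence.* Section 7.7 gives point prevalence in May and November. Section 6.1 puts peak transmission from May to October, so one survey falls at the start of the peak and the other after it. Season and drug effect cannot be separated.
- *Against the background rate.* The 3-6 attacks per child-year in section 6.1 is a general rural figure, not measured by this surveillance in these villages.
- *By number of courses received.* This would be non-randomised and is not planned in the protocol.

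**2. The plan's own sample size (section 7.4)**

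Inputs: p1 = 0.80, p0 = 0.45, between-village coefficient of variation k = 0.25, n = 60-100 children per village, 80% power, 5% level (taken as two-sided; the protocol does not say). Hayes-Bennett formula for unmatched clusters:

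c = 1 + (1.960 + 0.842)² × [p0(1−p0)/n + p1(1−p1)/n + k²(p0² + p1²)] / (p1 − p0)²

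For n = 80: 1 + 7.849 × [0.00309 + 0.00200 + 0.05266] / 0.1225 = 4.70. For n = 60 and n = 100 the results are 4.81 and 4.63. All round up to the stated 5 per arm, and power with 5 is 82-84%. The figure reproduces, but it sizes the trial for compliance only.

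**3. What the between-arm incidence contrast would show**

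Assumptions: equal background risk; incidence in an arm = base × (1 − coverage × E); the 80% and 45% of section 7.4 read as full coverage, with all other children unprotected. E is taken as 40% and 86%, the figures section 2.1 reports for SP and artesunate.

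R = (1 − 0.80E) / (1 − 0.45E)

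- E = 0.40: 0.680 / 0.820 = 0.83, an apparent reduction of 17%.
- E = 0.86: 0.312 / 0.613 = 0.51, an apparent reduction of 49%.
- Coverage 80% against 70%: R = 0.94 (E = 0.40) or 0.78 (E = 0.86).
- Equal coverage: R = 1.00 for any E.

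The same drug efficacy therefore gives very different contrasts, depending on the coverage gap.

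**4. Power for that contrast with 5 villages per arm**

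Further assumptions: a base rate of 2.1 to 4.2 attacks per child per season (70% of 3-6, section 6.1), 80 children per village, and the same k = 0.25 applied to incidence.

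v = (λ0 + λ1)/80 + k²(λ0² + λ1²); power = Φ{√[4(λ0 − λ1)²/v] − 1.960}

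For E = 0.40 and base 2.1: λ0 = 1.722, λ1 = 1.428, v = 0.0394 + 0.3128 = 0.352. The square root is √(4 × 0.0864/0.352) = 0.99, so power = Φ(−0.97) = 17%. Base 4.2 also gives 17%. Reaching 80% power would take 32-33 villages per arm. For E = 0.86, power is about 90% (0.895 and 0.918 at the two base rates).

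**The case against.** The strongest counter-argument is that the formula in step 3 inverts: E = (1 − R) / (0.80 − 0.45R). R = 0.829 returns 0.40 and R = 0.509 returns 0.86. A randomised gap in uptake, together with measured uptake, can thus identify efficacy indirectly, as an instrumental-variable analysis would. A reader might infer from this point that the objective is impossible to address in any form; that goes too far. What stands against the rescue is that the protocol does not plan it, and that it fails if coverage is equal. It also requires delivery route to affect recorded malaria only through drug uptake. Section 4.0 makes that doubtful, because the arms also differ in mobilisation and clinic contact, and section 7.9 detects cases at health centres. With five villages per arm the estimate would be imprecise.

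Three other stronger readings are tempting and are not supported:

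- *The report will credit a seasonal change in prevalence to IPTc.* No such analysis is stated. Section 7.13 specifies only the primary analysis, section 7.7 describes the May survey as baseline information, and section 5.2 lists parasitaemia at the end of the season, not a change.
- *The incidence result is meant to drive policy.* The AQ+SP efficacy sentence is funding-form text on capacity development. It is not an objective, end-point or analysis, and it does not refer to the incidence objective.
- *The dilution from 40-86% to 17-49% is a forecast.* Section 2.1 gives those efficacies for three courses of SP and artesunate, whereas this trial gives four courses of AQ+SP, for which the protocol cites no figure. Section 7.4 also allows facility compliance worse than 45%, which would widen the contrast.

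It is also fair to say that the end-point in section 5.2 is neutrally worded and can be measured in each arm.

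**Conclusion.** The point holds as a mismatch between one secondary objective and the design. The objective asks for the effect of IPTc on incidence, and no comparison in the protocol estimates that directly. This follows from the arms and the surveillance dates and does not depend on the arithmetic. The figures (ratio 0.83 to 0.51, or 1.00 at equal coverage; power about 17% at 40% efficacy) are illustrative. They rest on proportional protection, equal background risk, borrowed efficacies and a between-village variation that the protocol gives for compliance, not incidence.

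Severity is moderate. The primary objective, its end-point and the five villages per arm are unaffected, and the study describes itself as a pilot.

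**What to change.** - In section 3.0, replace the objective with: *To compare the incidence of clinical malaria, and the prevalence of parasitaemia at the end of the rainy season, between the two delivery systems.*
- State that the change in prevalence from May to November is descriptive and will not be attributed to IPTc.
- State that the incidence comparison is exploratory, because the trial was sized on compliance only.
- As a consistency edit, remove or soften the AQ+SP efficacy sentence under Training and Capacity Development.

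The cost is wording only: conduct, data collection, sample size and budget do not change. The trial gives up a claim that its design does not directly support. Keeping the present objective would instead require an untreated or pre-intervention incidence comparison, which is a change of design.
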